Method of comparison: Before/after comparison/parallel group comparison

Method of allocation of intervention: Randomization

Blinding of evaluators: Blinding of only the researcher in charge of statistical analysis.

Therefore, this study is a randomized controlled trial.

2) Method

Those who are willing to participate in the study, agree to participate after receiving a thorough oral and written explanation from the investigator, and meet the eligibility criteria will be enrolled as study subjects. Using an allocation chart, the study administrator will randomly assign the subjects to the SRI group or the control group and implement the intervention. Afterwards, only the subject's ID and data will be sent to the co-researcher in charge of statistical analysis, who will conduct the analysis. In this way, blinding the researcher in charge of statistical analysis minimizes bias and ensures appropriate results.

The flow of implementation is shown in Figure 1. The study consists of six phases: (a) preliminary investigation (screening), (b) initial evaluation, (c) evaluation immediately before the intervention, (d) intervention, (e) evaluation immediately after the intervention, and (f) final evaluation. Each phase is described below. All surveys, evaluations, and interventions will be conducted at Human Health Science, Graduate School of Medicine, Kyoto University.

[figure not shown]

Figure 1: Flow of Implementation

1. Preliminary investigation (screening)

The main purposes of this survey are to screen subjects who are not suitable for the study and to evaluate their psychiatric disorders and sensory processing characteristics. The items measured were (1) basic information of the subjects, (2) medical information, (3) JSI-mini (Japanese Sensory Inventory mini), (4) Autism spectrum Quotient (AQ), (5) Schizotypal Personality Questionnaire (SPQ), and (6) the Japanese Adolescent/Adult Sensory Profile (A/ASP) (see "3) Observation Items and Schedule"). If the eligibility criteria are not met, the subjects will be asked to refrain from further participation in the study, and the experiment will be terminated with an honorarium, based on the time spent in the preliminary investigation. After enrollment of study subjects who meet the eligibility criteria, the subjects will be randomly assigned to two groups, the SRI group and the control group, and will be blinded to the assigned researcher (in charge of statistical analysis) until the end of the analysis.

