1. Initial assessment

Following the preliminary survey, participants will be asked to participate in an initial evaluation. In the initial evaluation, you will be asked to complete (1) Cognitive Assessment Battery (CAB) . (See "3) Observation Items and Schedule"). This will serve as a standard for the temporal assessment of cognitive function of the study subjects before the intervention. This assessment will be conducted on the day before the intervention in order to reduce the burden on the research subjects and to provide potential control data for future multi-week intervention studies on people with mental disorders.

1. Evaluation before the intervention

　On the day following the initial evaluation, participants will participate in a pre-intervention evaluation before the intervention. The evaluation items will be (1) RSA measurement during the Sensory Challenge Protocol (SCP), (2) EEG measurement, and (3) Profile of Mood States 2nd Edition (POMS2). Because the RSA measurement, which is the main outcome of this study, will be conducted at the time point closest to the intervention, the measurements will be conducted in the order of POMS2, EEG, and RSA measurements. These assessments will be used as the basis for a longitudinal evaluation of the subjects' autonomic nervous system function and EEG waveform trends and subjective mood state before the intervention.

1. Intervention

The SRI (Sensory Room Intervention) group will receive an intervention using a sensory room, and the control group will receive 30 minutes of static activity. Of the 58 subjects in the study, approximately 20 subjects who gave their consent will undergo EEG, electrocardiogram (ECG), and pulse wave measurements to determine the degree of relaxation, cognitive activation, and sleep arousal during the intervention (Ref. 13).

≪ Intervention details.≫

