After the 30-minute intervention, a post-intervention evaluation was conducted. The evaluation items consist of (1) RSA measurement during the Sensory Challenge Protocol (SCP), (2) EEG measurement, and (3) Profile of Mood States 2nd Edition (POMS2), the same as the evaluation immediately before the intervention (see "3) Observation Items and Schedule"). The order of the procedures is RSA measurement, EEG measurement, and POMS2, in that order. The time required is approximately 60 minutes. We will examine how the intervention changes the subjects' autonomic nervous system function, EEG waveform trends, and subjective mood state in the intervention and control groups, respectively.

1. Final Evaluation

The day after the immediate post-intervention evaluation, the final evaluation will be conducted. The final evaluation will be conducted using the CAB (1) conducted in the initial evaluation (see "3) Observation Items and Schedule"). The time required is approximately 30 minutes. We will examine how the intervention changed the cognitive function of the subjects in the intervention group and the control group.

3) Observation, inspection, investigation, and reporting items and schedule

- Measurement item, measurement method, person or organization

The measurement items and methods are described below. All measurements are performed by the researcher.

1. Items to be conducted in the preliminary investigation

The following will be heard and evaluated. The time required is 30 minutes.

1. Basic information of the subjects (age, gender, educational and occupational history, handedness, intellectual function) (Ref. 3): The Japanese version of the FLANDERS Handedness Test (Ref. 4) is used to assess handedness, and the JART (Japanese Adult Reading Test) (Ref. 5) to assess intellectual function.
2. Medical information (history, current medical history, visual acuity, hearing, touch, taste, and smell) (Ref. 3): Visual acuity was assessed using the International Standardized Visual Acuity Test at 5 m, hearing using the Mimi Hearing Test, and touch using the Semmes-Weinstein monofilament.
3. JSI-mini (Japanese Sensory Inventory mini) (Ref. 2): A simplified version of the JSI-R (Japanese Sensory Inventory Revised), with 20 self-administered items. It is a simple way to grasp the tendency to receive sensory stimuli.

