The experimental flow is shown in Figure 2. The evaluation and intervention will be conducted over three days: on the first day, after explanation and consent, a preliminary survey and initial evaluation will be conducted; on the second day, the evaluation immediately before the intervention, the intervention, and the evaluation immediately after the intervention will be conducted; and on the third day, the final evaluation will be conducted. Each evaluation item will be conducted with appropriate breaks in between.

[figure not shown]

Figure 2: Measurement schedule

4) Summary of analysis

- - Primary Endpoint

(a) Differences in the variability of RSA values due to sensory stimulation of SCP before and after the intervention.

- - Secondary endpoint

(a) EEG amplitude differences before and after intervention, (b) POMS2 score differences before and after intervention, (c) CAB score differences at initial and final assessment, (d) correlation between AQ scores and RSA values, (e) correlation between SPQ scores and RSA values, (f) correlation between A/ASP scores and RSA values, (g) power spectrum by EEG band during intervention, (h) RSA power spectrum of each EEG band, (h) RSA during intervention

- - Main Analysis Methods

The statistical significance level is set at p < 0.05. A one-tailed test is used.

Basic information, medical information, and observation records during the use of the sensory room were compiled as descriptive statistics: RSA values were calculated as the difference between the SCP resting period and the mean value during each sensory stimulus; EEG amplitudes were obtained by subtracting the standard stimulus waveform from the deviant stimulus waveform of the presented task to obtain the amplitude of the positive or negative component during latencies of approximately 200 to 400 ms. The EEG amplitude is obtained by subtracting the standard stimulus waveform from the deviant stimulus waveform of the presented task.

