Unpaired t-tests will be conducted between the two groups to confirm the absence of any differences between the SRI and control groups in the baseline pretest, initial assessment, and the assessment immediately before the intervention. Next, we will compare the differences in RSA values, EEG amplitude, and POMS2 scores between the two groups at the immediately pre-intervention and immediately post-intervention assessments using an unpaired t-test. The differences in CAB scores between the initial and final assessments will be compared between groups using an unpaired t-test. If there is a significant difference between the two groups in the items measured at baseline, stratified or subgroup analyses will be conducted.

Additionally, correlation coefficients will be determined for the association between the AQ, SPQ, and A/ASP scores from the preliminary study and the differences in RSA values, EEG amplitude, and POMS2 scores at the time of the evaluation immediately before and immediately after the intervention. For cerebral blood flow, the difference between the mean values at the beginning and end of each 5-minute period in the two groups at the beginning and end of the intervention will be calculated and compared between the groups using an uncorrelated t-test.

For the measures during the intervention, t-tests with no correspondence between groups will be performed for the power spectrum per band of the EEG and the RSA.

6. Research period

1) Research subject enrollment period

　Four years from the date of approval by the head of the research institution.

2) Study subjects observation period

　　　The observation period for research subjects will be 3 days from the time of the preliminary survey.

3) Research implementation period

The research period is five years from the date of approval by the head of the research institution.

7. Procedure for obtaining informed consent ("IC")

Before the preliminary study, the subject will be fully informed about the study using a written explanation of the study. The measurement items, measurement time, intervention details, and non-invasive nature of the study will be explained, and the subject will then decide to participate of his/her own free will. The subject's consent to participate in the study and his/her signature constitute the informed consent procedure.

8. Handling of personal information, etc.

1) Types of personal information, such as materials and information handled in the research

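### Random assignment is described before all the baseline measurements, and nothing keeps the arm from subject or measuring researcher until baseline is complete

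*Protocol*

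**What the plan says.** **Order of events.** Section 5-2) lists six phases. Assignment is described under the first, the preliminary investigation (screening): "After enrollment of study subjects who meet the eligibility criteria, the subjects will be randomly assigned to two groups". The initial evaluation with the CAB comes next: "Following the preliminary survey, participants will be asked to participate in an initial evaluation". The measurement schedule in section 5-3) puts both on one day: "on the first day, after explanation and consent, a preliminary survey and initial evaluation will be conducted". The other baselines (POMS2, EEG, RSA) come a day later: "On the day following the initial evaluation, participants will participate in a pre-intervention evaluation before the intervention".

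**Who knows the arm.** Section 5-1) states: "Blinding of evaluators: Blinding of only the researcher in charge of statistical analysis". Section 5-3) adds: "All measurements are performed by the researcher". The opening paragraph of section 5-2) says that "the study administrator will randomly assign the subjects to the SRI group or the control group and implement the intervention", using an allocation chart. The text does not say when the arm becomes known to the subject or to the person measuring.

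**How the baselines are used.** Section 5-4) says "we will compare the differences in RSA values, EEG amplitude, and POMS2 scores between the two groups", from immediately before to immediately after the intervention, by unpaired t-test. CAB is treated the same way, from initial to final assessment. Tests are one-tailed at 0.05.

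**The concern.** In an open comparison of two activities, the measurements after treatment are inevitably taken with the arm known. The baseline need not be, and it is the one half of the change score that the design can fully protect. As the text stands, that protection is missing. A subject who expects the Sensory Room, or a sedentary task, may rate mood differently or put different effort into a cognitive test. A researcher who knows the arm may conduct the session differently. Any such shift enters the before-after difference and cannot then be separated from the effect of the intervention.

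The planned baseline t-tests do not repair this. They have little chance of detecting a small shift. If they did find a difference, it could not be put down to chance alone, because these baselines follow assignment.

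**Working it through.** **1. The plan's own figure.** Inputs from section 4-3): effect size 0.7, one-tailed alpha 0.05, beta 0.20, two equal groups, about 10% dropout. With n per arm, the unpaired t-test has 2n − 2 degrees of freedom and noncentrality d·√(n/2). At n = 26 the noncentrality is 0.7 × √13 = 2.52, the one-sided critical value on 50 df is 1.676, and the power is 0.801. The total is 2 × 26 = 52, and 52 / 0.9 = 57.8, rounded up to 58. The stated 52 and 58 are reproduced, and the timing of assignment does not affect them.

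**2. How a baseline shift enters the contrast.** The compared quantity is (post − pre) in the SRI arm minus (post − pre) in the control arm. If knowledge of the arm moves the SRI baseline by b and the post value does not carry the same movement, the contrast moves by −b. A baseline that looks better in the SRI arm therefore works against SRI, and one that looks worse works in its favour.

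**3. Size, as an assumption.** The protocol gives no figure for b. Let s be the resulting movement of the contrast in SDs of the change score, positive when it favours SRI. With no true effect, the rejection probability is that of a noncentral t with noncentrality s·√(n/2). For s = 0.2 and n = 26 this is 0.2 × 3.606 = 0.721.

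| Assumed s | One-sided type I error, 26 per arm | 29 per arm |
|---|---|---|
| −0.2 | 0.009 | 0.008 |
| 0 | 0.050 | 0.050 |
| 0.1 | 0.099 | 0.102 |
| 0.2 | 0.175 | 0.186 |
| 0.3 | 0.282 | 0.303 |

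A shift of 0.2 is 0.2 / 0.7 = 29% of the planned effect. In the unfavourable direction the cost is power: a true effect of 0.7 would appear as 0.7 − 0.2 = 0.5, and power at 26 per arm would fall from 0.801 to 0.553.

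**4. If the shift is measured in SDs of a single measurement.** The SD of change is SD × √(2(1 − ρ)), where ρ is the pre-post correlation (assumed, not in the protocol). A favourable shift of 0.2 SD gives:
- ρ = 0.3: 0.2 / 1.183 = 0.169, type I error 0.148
- ρ = 0.5: 0.2 / 1.000 = 0.200, type I error 0.175
- ρ = 0.7: 0.2 / 0.775 = 0.258, type I error 0.234

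**5. Which outcomes are exposed.** Section 5-4) defines the RSA value as the difference between the resting period and the mean during each stimulus, and the EEG amplitude as the deviant waveform minus the standard waveform. Both are formed within one session. A general change in arousal that moves both parts equally cancels; only a change in the response to the stimuli remains. POMS2 and CAB scores have no such cancellation.

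**6. The planned baseline check.** At 29 per arm, a one-tailed test in the right direction detects a 0.2 SD difference in the tested measure with probability 0.186, by the same formula as in step 3.

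**The case against.** The strongest reply is that assigning early is not disclosing early. The allocation chart is with the study administrator, and the protocol does not say that the subject or the measuring researcher learns the arm before baseline. A reader might infer that the baselines are taken by staff who know the arm, or that the same therapist measures and treats a given subject. The text supports neither inference. Section 9-4) reserves both tasks for occupational therapists, but does not say that one person does both. This objection stands, and it makes the bias possible rather than established. The absence of any statement is still the weakness, since blinding is expressly limited to the analyst.

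The timing itself is also partly inferred. Enrolment fixes only the earliest moment for assignment, the opening paragraph of section 5-2) mentions assignment next to the intervention, and Figures 1 and 2 were not available for this check. The only text that places assignment in a phase nevertheless puts it in screening, and no other sentence moves it.

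A reader might also infer that the primary RSA endpoint takes any shift in full, or that the bias must create a false benefit. The documents do not support either reading. RSA reactivity is a within-session difference, so part of a shift may cancel. Subjects looking forward to the Sensory Room could start with better mood, which would shrink their apparent gain.

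Finally, measurements after the intervention remain open whatever is done at baseline. That is true and limits the benefit of the change, but it is no reason to leave the baseline exposed.

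**Conclusion.** The point holds as a gap in protection, not as demonstrated bias. As written, assignment precedes the baseline CAB, POMS2, EEG and RSA, only the analyst is blinded, and nothing withholds the arm from subject or measuring researcher until baseline is complete. Knowledge of the arm could therefore affect the baseline half of these change scores, in either direction. POMS2 and CAB, both secondary, are most exposed; the primary RSA endpoint and EEG are less so. The questionnaires completed at screening are not affected.

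The size cannot be derived from the documents. The move from 0.05 to about 0.175 or about 0.009 rests on an assumed shift of 0.2 SD of the change score, 26 per arm, and no equal shift in the post measurement. It shows sensitivity and is not an estimate. The change is worth making because it closes this route at almost no cost.

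**What to change.** In section 5-2), state that the assignment is made, or that a concealed assignment held by the study administrator is opened, only after the day 2 pre-intervention RSA measurement and before the intervention. State also that neither the subject nor the measuring researcher knows the arm before then. Amend the sentence on assignment under the preliminary investigation to match, and bring Figures 1 and 2 into line if they show otherwise.

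Either version protects the baseline. Nothing in the text requires earlier disclosure: the A/ASP that guides the Sensory Room session is scored for everyone at screening, and both arms use the same room. If assignment itself is moved, subjects who withdraw between day 1 and day 2 also cease to be losses after randomisation. The protocol does not split its 10% dropout by time, so that gain cannot be quantified.

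The cost is a short protocol amendment and a few minutes of room set-up between RSA and the intervention. Section 5-2) wants RSA as close to the intervention as possible, so the gap should be kept short and the same in both arms. The sample size stays at 52, then 58, and no extra staff are needed. Post-intervention measurements remain unblinded.

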The research question is: Does a sensory room intervention increase parasympathetic activity and EEG amplitude, and improve mood state and cognitive function compared to static activity in healthy adults?

1. What is the medical and social significance?

The uniqueness of this study lies in demonstrating the therapeutic effects of the Sensory Room through changes in physiological indices, such as autonomic nervous system function and EEG activity, as well as cognitive function. We believe that demonstrating the usefulness of the Sensory Room in healthy subjects through objective measures and improved cognitive function will greatly contribute to proposing a new treatment method for people with psychiatric disorders, of which a high percentage are believed to suffer from sensory processing disorders. In the future, the effectiveness of the Sensory Room is expected to be widely publicized, leading to its installation in hospitals, educational institutions, and workplaces, and to the improvement of mental health care and work efficiency for people with developmental disabilities and mental disorders as well as healthy people. In addition, the role of occupational therapists and the usefulness of occupational therapy in making the above contributions will be clarified.

4. How to select research subjects

1. setting

We will collect the subjects by posting information and distributing flyers (Ref.1) to healthy adults, undergraduate and graduate students living in the community, and others who inquire about this research, explaining the contents of this research orally and in writing.

1. Eligibility Criteria

　　Persons who meet all of the following selection criteria and none of the exclusion criteria will be enrolled as eligible.

Selection Criteria

1. The patient must be between 18 and 65 years of age at the time of registration.
2. Written consent to participate in the research has been obtained from the research subjects themselves.
3. Total score of 1 or more points on the JSI-mini (Japanese Sensory Inventory mini) (Ref.2)

The rationale for setting the age of the subjects (a) is that the subjects of this study are adults and that the decline in physical and mental functions due to old age may affect the results of the study. The reason for (c) was to target people who have some characteristics of sensory processing in their daily lives, which is the intervention target of this study.

Exclusion Criteria

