Persons who fall into any of the following categories shall not be used as research subjects.

1. Complications of cardiac disease.
2. Cardiac pacemaker users
3. History of epilepsy
4. Visual acuity (correctable) less than 0.7 in both eyes
5. Air conduction hearing greater than 30㏈.
6. There is tactile hypoesthesia (unable to perceive Semmes-Weinstein monofilament no. 2.83)
7. Perceived significant taste and olfactory abnormalities
8. History of any other visual or hearing impairment, language comprehension disorder, mental disorder, or motor dysfunction that would interfere with the performance of the research task.

The reasons for setting (a) and (b) are because they may affect autonomic measurements and (c) because they may affect electroencephalography measurements. The reason for (d) through (g) is to exclude people with functional abnormalities in the sensory organs to be evaluated and intervened in this study.

Suspension Criteria

1. When the research subject wishes to discontinue
2. When it is deemed appropriate to discontinue other activities.

3) Number of research subjects and rationale for setting the number of research subjects

The target number of patients for this study is 58, consisting of 29 in the intervention group and 29 in the control group.

Regarding the rationale for the setting, this study will conduct a two-group comparison (unpaired t-test, one-tailed) of the intervention and control groups for changes in the parasympathetic index (RSA: respiratory sinus arrhythmia) before and after the intervention as the main outcome. Using G*Power 3.1.9.2 and referring to previous studies^11)12)^ that utilized RSA, the effect size was set to 0.7, with an alpha error of 0.05 and a beta error of 0.20, resulting in a total sample size of 52 participants. In addition, considering the possibility of approximately 10% dropout, approximately 58 subjects will be needed for the study. 58 subjects will be randomly divided into 29 in the SRI group and 29 in the control group.

The number of subjects in the previous study^6)13)^, which investigated parasympathetic indices and sensory processing characteristics in children with ASD and normal children, was 50 and 83, respectively, and we believe that the above number of subjects is generally appropriate.

5. Method of the study and the scientific rationale for the study

1) Design

□ Intervention study

Phase of study: Exploratory study

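### The blanket one-tailed rule is wrong for the baseline checks and other tests with no stated direction, and the tail is not operationally defined for RSA and EEG amplitude

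*Protocol*

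**What the plan says.** Section 5, 4), Main Analysis Methods, fixes level and sidedness in one place for all analyses: "The statistical significance level is set at p < 0.05. A one-tailed test is used". Section 4, 3) repeats this for the primary outcome, where "this study will conduct a two-group comparison (unpaired t-test, one-tailed) of the intervention and control groups for changes in the parasympathetic index" is the basis of the sample size. There "the effect size was set to 0.7, with an alpha error of 0.05 and a beta error of 0.20", which gives 52 in total, raised to 58 for dropout.

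The same analysis section then lists these tests:

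- **Baseline.** "Unpaired t-tests will be conducted between the two groups to confirm the absence of any differences between the SRI and control groups". A significant baseline difference leads to stratified or subgroup analyses.
- **Pre-post changes.** RSA, EEG amplitude, POMS2 and CAB changes are compared between groups.
- **Correlations.** AQ, SPQ and A/ASP scores are correlated with the changes in RSA, EEG amplitude and POMS2.
- **Other group comparisons.** Cerebral blood flow, and EEG band power and RSA during the intervention, are compared between groups.

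Section 3 gives a direction for the main outcomes through its research question: "Does a sensory room intervention increase parasympathetic activity and EEG amplitude, and improve mood state and cognitive function compared to static activity in healthy adults".

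**The concern.** A one-tailed test needs a direction fixed before the data are seen, and a reason to treat the opposite result as no finding. The protocol applies the rule to comparisons that have neither.

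The baseline checks ask about differences of either sign, and their result decides whether stratified or subgroup analyses are run. A one-tailed check would set off that step for an imbalance in one direction and stay silent for an equal imbalance in the other.

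For band power, cerebral blood flow and the trait correlations, someone has to pick a tail. Nothing in the protocol stops that choice from following the data.

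For RSA and EEG amplitude the direction is stated only for the construct. The analysed RSA quantity is a difference between the resting period and each stimulus. The order of subtraction is not given, nor is it said whether a larger or a smaller response to stimulation counts as greater parasympathetic activity. The EEG component may be positive or negative, so an increase in amplitude has no fixed sign.

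**Working it through.** **Inputs.** Section 4, 3): d = 0.7, alpha 0.05 one-tailed, power 0.80, 52 evaluable (26 per arm), about 10% dropout, 58 enrolled (29 per arm). The protocol gives no pre-post correlation, so a range is assumed in step 5.

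**Formula.** For a two-sample t-test with n per arm, df = 2n − 2 and the noncentrality is d × √(n/2). One-tailed power is the probability that a noncentral t exceeds the 0.95 quantile of t. Two-tailed power uses the 0.975 quantile and counts both tails.

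**1. The plan's own figure.** With n = 26 the noncentrality is 0.7 × √13 = 2.524, df = 50, and the one-tailed critical value is 1.676. Power is 0.801, so 26 per arm (52 in total) reproduces. 52 / 0.9 = 57.8, so 58 reproduces. Both hold only for the one-tailed test.

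**2. Baseline check, all 29 per arm.** For a true imbalance of 0.7 SD the noncentrality is 0.7 × √14.5 = 2.666, df = 56, and the critical value is 1.673.

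| True imbalance | One-tailed 0.05 | Two-tailed 0.05 |
|---|---|---|
| 0.7 SD, chosen direction | 83.8% | 74.5% |
| 0.7 SD, other direction | about 0.001% | 74.5% |

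**3. False-positive rate.** 200,000 simulated null trials with 26 per arm gave:

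| Procedure | Rejection rate |
|---|---|
| One-tailed 0.05, direction fixed beforehand | 0.0501 |
| One-tailed 0.05, tail picked after seeing the data | 0.1002 |
| Two-tailed 0.05, both directions | 0.0500 |
| Two-tailed 0.05, favourable direction only | 0.0251 |

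A result just at the one-tailed critical value of 1.676 has a two-tailed p of 0.10. The two-tailed critical value is 2.009.

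**4. Primary test made two-tailed, d = 0.7.** Power is 69.7% with 26 per arm and 74.5% with 29 per arm. The d detectable with 80% power at 26 per arm rises from 0.70 to 0.79. Holding 80% power at d = 0.7 needs 34 per arm, which is 68 evaluable; 68 / 0.9 = 75.6, so 76 enrolled.

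**5. Baseline-adjusted alternative.** If 0.7 is the standardised effect on the change score, and variances are equal before and after with correlation ρ, adjustment for the pre-value gives an effective d of 0.7 / √((1 + ρ)/2). Two-tailed, 26 per arm:

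| Assumed ρ | Effective d | Power |
|---|---|---|
| 0.3 | 0.868 | 87% |
| 0.5 | 0.808 | 82% |
| 0.6 | 0.783 | 79% |
| 0.7 | 0.759 | 77% |
| 0.8 | 0.738 | 74% |

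**The case against.** The strongest defence is that the primary test is coherent. Section 3 states the expected direction for parasympathetic activity, EEG amplitude, mood and cognition. Section 4, 3) declares a one-tailed test and sizes the trial on it correctly. The study is labelled exploratory. A pre-declared one-tailed test at 0.05 has 5% error, and whether that is strict enough is a matter of convention. This stands.

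Three stronger readings are tempting, and the document does not support them:

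- **That the rule doubles the false-positive rate of every test.** For outcomes with a stated direction the rate is the declared 5%. It is double only against the 2.5% that a two-tailed test allows in the favourable direction. The 10% figure needs a tail picked after seeing the data.
- **That the trial could not report an adverse effect.** A fall in RSA or a worsening of mood could still be estimated and described. It could not be declared significant.
- **That no EEG contrast has a predicted direction.** Amplitude has one. Band power does not.

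It is also fair to say that the protocol names no test for the correlations, so one-tailed testing of them is only an inference from the general rule.

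The defence does not reach the baseline checks, band power or cerebral blood flow. Nor does it supply the missing RSA sign or EEG polarity.

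**Conclusion.** The point holds in a limited form. As written, the rule gives wrong results for the baseline checks: a 0.7 SD imbalance is found about 84% of the time in one direction and practically never in the other, and the outcome changes which analyses are run. The 0.7 SD is illustrative, borrowed from the protocol's effect size. The rule cannot properly apply to band power or cerebral blood flow, nor to the trait correlations if they are tested, because no direction is stated. If the tail follows the data there, error is 10% per test.

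For RSA, EEG amplitude, POMS2 and CAB the declared 5% error stands. For RSA and EEG amplitude it does so only once the sign that counts as benefit is defined, which the protocol has not done. The sample size of 52, raised to 58, is correct for the test it declares.

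A reader might infer that two-tailed testing costs nothing because baseline adjustment restores the power. That depends on a correlation the protocol does not give: power is 82% if it is 0.5, but 79% at 0.6 and 74% at 0.8.

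**What to change.** 1. In Main Analysis Methods, limit the one-tailed rule. Make every test without a pre-stated direction two-tailed at 0.05: the baseline comparisons, band power during the session, cerebral blood flow, and the correlations if tested. Report effects with 95% confidence intervals.
2. State the order of subtraction for the RSA difference and which sign of the between-group contrast counts as benefit. State the polarity of the EEG component and what an increase in amplitude means for it.
3. For the primary RSA test choose one option:
   - (a) keep it one-tailed, with the sign from item 2 and a written justification; 52 and 58 then stand; or
   - (b) make it two-tailed, keep 58, and restate power in section 4, 3) as about 70% at d = 0.7 with 26 per arm (74.5% with 29 per arm; detectable d 0.79 at 80% power with 26 per arm).
4. If a baseline-adjusted analysis is adopted, state its power over a range of assumed correlations, as in step 5 of the working, and do not present it as recovering 80%.

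Items 1 and 2 and option (a) are wording changes. Option (b) costs a less favourable stated power, or enrolment of 76 if 80% is to be kept with the unadjusted test. Item 4 replaces the planned t-test and so is a change of analysis method.
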